
#### Empathy and compassion

We will also examine pre-post changes in empathy and compassion in the 3 intervention groups. It has long been argued that engaging in mindfulness practice can increase empathic functioning [147–150]. However, previous findings on the effects of mindfulness interventions are somewhat inconsistent. More specifically, they suggest differential effects of different types of practices on affective and cognitive aspects of empathic functioning, and highlight shortcomings in the use of self-report measures of empathy [151]. In the ReSource project, a specific task was developed, the EmpaToM, to test differential effects of different mental training modules on different aspects of socio-emotional and socio-cognitive functioning such as empathy, compassion and Theory of Mind [152]. And indeed, while the socio-affective training module (Affect) was most efficient in improving compassion, the socio-cognitive module (Perspective) was unrivaled in improving Theory of Mind, also called cognitive empathy or cognitive perspective taking [71]. Thus, we will also employ the EmpaToM to assess differential effects of the two different intervention groups on social emotions and cognition. More specifically, based on previous evidence, a training related increase in compassion can be expected specifically for the socio-emotional ‘Affect Dyad’ intervention, whereas none of the interventions should induce any changes in Theory of Mind [71]. This expected increase in compassion does not only apply to compassion for others, but also to self-compassion [153]. With regard to empathy, the predictions are more complex, since previous research has clearly shown differential behavioral, subjective and neuronal patterns and mechanisms underlying empathy and compassion [154–156]. While compassion is based on care and affiliative motivational systems, it is mostly associated with positive affect and warmth, and promotes resilience, empathy, being broadly defined as affect sharing [157]. However, this can also induce negative affect, and even turn into intense feelings of anxiety and dysphoric mood, specifically when a healthy distinction between the self and others is not given [156]. Accordingly, the concept of “empathic distress” is a self-focused component of empathic functioning that indicates a strong and aversive reaction to the suffering of somebody else. Particularly, excessive altruism can lead to empathic distress fatigue, a state of burnout that relates to the regular exposure to others’ suffering [158]. It has previously been found that empathic distress decreases in individuals who undergo MBSR and compassion trainings [89, 159]. It is expected that the compassion-based socio-emotional mental training is thus decreasing empathic distress aspects while increasing positive affect and (self)compassion. At the same time, the socio-emotional dyadic training is aiming at increasing empathic listening and with that the healthy component of empathy. Furthermore, while underlying mechanisms remain largely unknown, differential changes in affect, thought patterns and emotion regulation strategies are also suggested to mediate differential intervention effects on empathy and compassion [160]. Thus, we would expect more positive other-related thoughts and more positive low-arousal affect after socio-emotional training. Besides, augmented interoceptive awareness, i.e., specifically, an increase in using the body for self-regulation, has been associated with mindfulness-based mental trainings such as the Presence module of the ReSource project that require individuals to focus on bodily sensations [83]. Previous research has repeatedly shown a positive association between interoceptive body awareness, alexithymia and empathy, which are mediated through function of the anterior insular cortex [161–163]. Using different interoceptive body awareness and regulation measures in the ReSource project, Bornemann et al. [83–85] could show that different types of mental training can indeed increase interoceptive body awareness over the training of several months, and that this increase in interoceptive body awareness and regulation goes along with a decrease in alexithymia and better emotion understanding (see also [164]). Interestingly, these training-related increases were observed both after mindfulness-based as well as socio-emotional trainings, therefore suggesting that an increase in interoceptive awareness will be a meaningful mediation mechanism in both intervention groups. We will further examine changes in mediators using the daily and weekly EMA approaches, employing a variety of validated questionnaires (please see Measures section).

#### Prosocial behavior

We will also investigate differential impacts of the socio-emotional and mindfulness-based intervention on altruistic prosocial behavior. Based on previous findings [74, 165, 166], we expect that altruistic prosocial behavior will uniquely increase as a result of the care and compassion-based socio-emotional mental training. We will employ the Zurich Prosocial Game (ZPG) [166] and monetary distribution tasks that are suitable to measure altruistic behavior (i.e., Social Value Orientation, Social Discounting questionnaire) to test differential effects of mindfulness-based and socio-emotional mental trainings. Since altruistic prosocial behavior is based on a specific set of motivations that are directed towards caring for others [74, 167, 168], we will investigate whether intervention-related increases in compassion mediate these effects. We further expect that the decrease in empathic distress (see above) and a concomitant increase in positive affect and other-related thought patterns will mediate training-related increases in altruistic prosocial behavior (similar to compassion). Since empathy and compassion can be considered essential for successful and beneficial social interactions [157, 169], and compassion training may be a useful tool in promoting social relationships [170], we will test a mediating role of frequency and quality of social interactions in a training-related effect on prosocial behavior. We will examine changes in mediators using the daily and weekly EMA approaches, employing a variety of validated questionnaires (please see Measures section).

#### Epigenetic markers

We will also examine the impact of intervention-related changes in epigenetic markers associated with mental health, resilience and social capacities from pre- to post-intervention. Changes in psychopathology and resilience as a consequence of stress exposure can also be reflected in terms of changes in epigenome, such that transcription factor activation embedded by gene regulation and expression changes over time [171]. Epigenetic changes affect the gene transcription, not by changing the genome sequence, but by changing the accessibility of transcription regulators (e.g., DNA methylation, histone modifications; [172]. In conditions of chronic stress, glucocorticoids acting as transcription factors play a prominent role in inducing permanent epigenetic changes, which is evident through enrichment of the DNA methylation site of the glucocorticoid response in stress-related epigenetic changes [173]. These environment-dependent epigenetic changes are further influenced by genetic factors, such that genes, environment and epigenetics come together to produce changes [174]. Several studies have shown changes in DNA methylation following interventions for various disorders such as depression and post-traumatic stress disorder [175–177]. Therefore, intervention-related changes in polyepigenetic risk markers will be evaluated pre- to post-intervention in the present study.

#### Inflammation

In addition to neuroendocrine and epigenetic markers of stress during the SARS-CoV-2 pandemic, we will assess a marker of systemic inflammation, i.e., salivary levels of C-reactive protein (CRP), an acute phase protein that signals activation of pro-inflammatory pathways. During acute stress, the brain responds with a robust inflammatory response, both centrally and in the periphery, likely to ensure survival during threat of injury [178, 179]. Psychosocial laboratory stress alone has been shown to induce a potent increase in the secretion of pro-inflammatory cytokines, such as IL-6 and TNF-a, via autonomic nervous system activation and induction of NFkB signaling in immune cells [180, 181]. Glucocorticoids released during stress can exert inhibitory effects on innate immune responses. During chronic stress, however, the glucocorticoid receptor (GR) may become resistant to the regulatory effects of glucocorticoids, likely in part due to ever-expression of FKBP51 protein [182], further promoting pro-inflammatory activation [183, 184]. There are numerous reports documenting increased low-grade systemic inflammation in individuals living under conditions of chronic stress [179] and, especially, loneliness or social isolation [22]. In addition, systemic inflammation is one of the best-replicated findings in children and adults exposed to early adversity [185]. It has been suggested that peripheral cytokines may cross the blood-brain barrier, promoting neuroinflammation and further potentiating stress responses, with ultimate impact on structure and function of neural circuits implicated in behaviors of depression and anxiety [183]. Accordingly, increased levels of systemic inflammation are a cardinal feature of patients with major depression and certain anxiety disorders [186]. Anti-inflammatory medication is considered a viable treatment for affective symptoms in immune-based depression [187]. In addition, psychosocial interventions and meditation may lower systemic inflammation as a final common pathway [188]. Here, we test 1) whether chronic stress related to the SARS-Cov-2 pandemic, as assessed over the course of the pandemic and associated lockdowns, is associated with increased levels of systemic inflammation, i.e., salivary CRP concentrations, 2*)* whether this increase is accentuated in individuals with early life adversity, and 3) whether the dyadic intervention ameliorates systemic inflammation with impact on mental and physical well-being. We will explore associations of inflammation with neuroendocrine and epigenetic indices of stress, symptoms and treatment response, as well as GxE interactions.

The current study is the second phase of the larger CovSocial project, which previously in its first phase assessed a sample of Berliners on changes in various aspects of mental health, resilience and social cohesion over the course of the pandemic in Berlin, Germany from January 2020 to March 2021 (please see our preregistration for the first phase on Open Science Framework osf.io/jvb98). This allows us to incorporate extensive information about individual longitudinal change patterns in vulnerability, resilience and social cohesion over the period of more than a year during the SARS-CoV-2 pandemic. A broad range of state indicators of those constructs was assessed for 7 timepoints over a period lasting more than a year, from January 2020 to March 2021. In the first phase of the project, participants also provided self-report assessments of personality and behavioral traits (trait) associated with higher vulnerability to stress and mental health problems, resilience and social cohesion. The current study will be conducted in a sub-sample of the participants assessed in phase 1. Please see Fig 1 for a depiction of the sample recruitment for phase 1, detailing dropouts from registration to the completion of the first three timepoints of the first phase of the study. Also, please see Fig 2 for an overview of the schedule of enrolment, interventions, and assessments. Therefore, the longitudinal assessment of mental health, resilience and social cohesion factors from phase 1 of the project, along with the trait measures assessed in phase 1, will also be used to predict both pre-test status and intervention-related changes from pre- to post-test in our variables of interest in phase 2 in an exploratory manner.

**Fig 1 pone.0256323.g001:**
[figure not shown]
A depiction of the recruited sample, dropouts at every stage of the first phase of the study, and the process of reaching the final sample. Sample 1 indicates the final sample of participants that completed the first three assessment timepoints (T1-T3).

**Fig 2 pone.0256323.g002:**
[figure not shown]
An overview of the schedule of enrollment, interventions, and assessments.

Furthermore, during the first phase in December 2020, we assessed genome-wide markers to calculate polygenic risk scores in a sub-sample of participants of phase1, and we will evaluate the predictive impact of these markers on pre-test status and intervention-related changes in our variables of interest during the current second phase (using phase 1 or phase 2 genotype data).

Lastly, we will also explore the directional and temporal interplay between the changes in the different mediator variables mentioned in the sections above. Finally, we will also explore the effects of important socio-demographic factors (age, gender, income, education in years, marital status, number of children etc.) and other context variables including COVID-19 related questions (e.g., access to green spaces, job status, covid-related health status, living situation, financial and job risk factors) on pre-test status and the intervention-related changes. For a detailed overview of the hypotheses of the current study, please see our preregistration on the Open Science Framework (osf.io/32c5q). For an overview of the phase 2 of the CovSocial project, please see Fig 3.

**Fig 3 pone.0256323.g003:**
[figure not shown]
An overview of the study design of phase 2 of the CovSocial project.

## Materials and methods

### Sample and sampling procedure

Participants for the current study will be selected from a community sample of participants from Berlin, Germany that were recruited for the first phase of the CovSocial project (Details of the study site can be obtained from the ClinicalTrials.gov by accessing the study record at https://clinicaltrials.gov/ct2/show/NCT04889508). Participants for the first phase of the project were recruited from the population of the city of Berlin, Germany. The main inclusion criteria involved being between 18 and 65 years of age, being able to understand the German language, and to be registered as a resident of the city of Berlin at the time of the assessment. We used a variety of methods for recruitment including sampling 56,000 individuals from the Berlin registration office, flyers and posters, and advertising on social media, in addition to the chain-referral method. The recruitment led to the registration of 7214 individuals to take part in the study. Out of this, only 5877 started the questionnaires, and at every block of questionnaires we saw further dropout in sample. A total of 3681 individuals completed the questionnaires for the first three timepoints of the first phase of the study. Lastly, participants were excluded for not meeting the inclusion criteria and for data quality reasons, leading to a final sample of 3522 individuals for the first three timepoints of the first phase of the project. Please see S1 Appendix for the number of participants at each further timepoint T4-T7, and all participants who also completed the genome-wide marker assessment.

Participants for the second phase will now be recruited from this initial sample, and assigned to one of the three groups, socio-emotional intervention group, mindfulness-based intervention group, and retest control group (waitlist control), in the following sequential steps (please see Fig 4).

**Fig 4 pone.0256323.g004:**
[figure not shown]
The sampling and randomization procedure.

First, all participants with completed data sets at the first three timepoints of retrospective longitudinal assessments in phase 1 (T1-T3; *n* = 3522) will be invited to complete a pre-screening to assess whether they qualify to take part in the current study based on the inclusion and exclusion criteria. They will be asked to give informed consent for this pre-screening assessment prior to completing the pre-screening questionnaire.Based on the pre-screening, participants will be selected to take part in the study based on the following inclusion and exclusion criteria.
Participants will have to meet the following inclusion criteria: between 18- and 65-years age, resident of Berlin, and proficiency in German language.Participants will be excluded if they do not have access to internet or the necessary technical equipment, if they have an educational background in psychology, if they have regular spiritual practice (including yoga practice with meditative component), if they take medication that influences physiological markers or if they take psychiatric medication, if they have participated in stress reduction programs previously, if they suffer from chronic illness or pain, or if they have a history of or current psychiatric diagnosis. Further, participants will be excluded based on the cut-off scores for the following questionnaires: Toronto Alexithymia Scale-20 (TAS-20; [189, 190]); exclude if score greater than 60), Patient Health Questionnaire-9 (PHQ-9; [190]); exclude if scores greater than 19), and Generalized Anxiety Disorder-7 (GAD-7; [191]); exclude if scores greater than 15). Participants endorsing suicidality on the PHQ-9 will also be excluded.In a third step, individuals who meet all the inclusion and exclusion criteria will be randomly assigned to one of three groups. Initially, the three groups will be oversampled, to ideally form *n* = 200 per group.In the next step all these individuals will be invited to take part in online informational webinars about the study. These online events will serve the purpose of providing interested individuals with information about mindfulness meditation and concepts underlying the socio-emotional mental training. Further, information about exact dates and study procedures will be given. After this event, individuals will have to indicate their interest in participating in the study.In case, the number of interested individuals is higher than the targeted *n* = 100 per group, then the extra number of interested individuals will be excluded based upon study-relevant considerations to make sure that we have three comparable final groups with *n* = 100 each. The participants will then complete the written informed consent indicating their consent to participate in the study.Next, individuals who provide informed consent to take part in the study will undergo screening phone calls with licensed mindfulness-based meditation instructors. In these individual calls, participants will undergo mental health screening using the Standardized Assessment of Severity of Personality Disorder-Abbreviated Scale [192] and the Composite International Diagnostic-Screener [193]. These screening calls would further allow us to exclude individuals who are evaluated as meeting criteria for clinical diagnoses or psychological instability as identified by the meditation instructors, using the screening instruments. This is an important step as the current study is a first step towards exploring the effects of low-intensity online socio-emotional interventions in a non-clinical population. In future studies, this line of research may be extended to clinical populations.astly, if based on the above-mentioned individual screening calls with meditation teachers some individuals have to still be excluded from the study, then the above sampling procedure will be repeated in order to fill any participant gaps in each group.

An estimated 300 individuals, 100 per intervention group, will be recruited. A priori effect size and power calculations have been performed based on the results from the previous mental training study, the ReSource project [67], which developed and validated the interventions being applied in the current study. Power analyses were conducted using G*Power [194] for analysis of variance with repeated measurements and interactions between group and intra-group variables. The analyses elements were as follows: an alpha level of .05, with a power (1-ß) of .80, 3 groups and 2 measurement occasions, a correlation of variables with repeated measurements of .39 which is the lower limit of retest reliability for the Cortisol Awakening Response (CAR; [195]), and an assumed small effect size of *f* = .10. This results in a total sample size of *n* = 297. For the additional third measurement time (post-test 2 following socio-emotional intervention given to waitlist control group) power analysis was conducted in a similar manner as above.

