### Procedure

The study will begin with the invitation of Berliners who took part in the first phase of the CovSocial project. The invitation for the current study will include brief information about the current second phase of the project, and the link to complete the online pre-screening questionnaire. Once interested individuals complete the prescreening, the results from the questionnaire will be analyzed to select the appropriate individuals who meet the inclusion and exclusion criteria (listed in the sample section above). The selected individuals will be randomly assigned to form three tentative groups with *n* = 200 each, socio-emotional intervention group, mindfulness-based intervention group, and retest control group (waitlist control). These selected individuals will then be invited to an online information webinar for further detailed information about the study, including introduction to the specific intervention they have been randomly assigned. Upon the webinars, individuals who express interest in taking part in the study will receive an email to formally sign up for the study by providing formal informed consent, in order to form final three *n* = 100 groups. The participants will then undergo short 30-minute screening calls with MBSR instructors, who will ultimately also track the progress of participants throughout the course of the intervention with weekly check-in meetings. After the screening calls, a final assessment of the three groups will take place, and further participants will be recruited in case of dropouts to make sure that we have *n* = 100 per group. This will complete the recruitment procedure which will take place entirely online.

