After the recruitment, participants will complete a 2-week pre-intervention EMA, wherein they will provide saliva samples at specific timepoints and answer questions about their mental and physical health during those corresponding timepoints. This period of data collection will take place at the convenience of participants (at their home, workplace, etc.) to be able to capture the ecologically valid CAR and stress response. For this portion, participants will be sent the appropriate saliva collection kits by mail. Next, all participants will then be invited to the lab to complete the pre-intervention assessment of the behavioral tasks, and they will also complete the pre-intervention assessment of questionnaires using the web and mobile App. This pre-intervention assessment period will last approximately 4 weeks, after which the intervention period will begin.

The intervention period will last 10 weeks, and no blinding will be employed During each week participants in the two intervention groups will perform the intervention-specific exercises 6 times a week using the mobile or web app designed for the study. Every day prior to and after completing the intervention exercise, participants will complete the intervention-related daily EMA using app. Once a week, participants will undergo 2-hour online coaching sessions with an intervention instructor. The purpose of these so-called “weekly check-ins” would be to ensure that participants are able to share insights gained during the week, resolve issues faced during the week, and to keep up the motivation and commitment of participants. Once a week, at a random timepoint, participants will also complete the weekly assessment measures tracking changes in various potential mechanistic variables of interest using the app. During this first intervention period, participants in the retest control group will not complete any daily EMA or weekly assessments. After the completion of the first 10-week intervention period, all participants will again be invited to the lab to complete the same battery of behavioral tasks at post-intervention, and will also complete the same battery of questionnaires through the web and mobile App. Participants will once again undergo a 2-week post-intervention EMA period, during which they will provide saliva samples at specific timepoints, along with answering questions about mental and physical health at those timepoints.

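### Random assignment precedes arm disclosure, consent, trimming and screening, so the roughly 100 per arm analysed are no longer fully protected by randomisation

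*Protocol article*

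**What the plan says.** The order of steps is set out in the protocol article under Sample and sampling procedure (the steps accompanying Fig 4) and again under Procedure.

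- Assignment follows the online pre-screening: "individuals who meet all the inclusion and exclusion criteria will be randomly assigned to one of three groups". Procedure gives the same point and calls the groups provisional: "The selected individuals will be randomly assigned to form three tentative groups", with 200 in each. Sample and sampling procedure describes 200 as an ideal.
- A webinar follows. Sample and sampling procedure describes general content on both training approaches, plus dates and procedures. Procedure adds that it covers the arm drawn: "including introduction to the specific intervention they have been randomly assigned".
- People then opt in or out: "After this event, individuals will have to indicate their interest in participating in the study".
- If more than 100 in a group are interested, "the extra number of interested individuals will be excluded based upon study-relevant considerations to make sure that we have three comparable final groups".
- Only then comes study consent: "The participants will then complete the written informed consent indicating their consent to participate in the study".
- A screening call follows. Instructors may exclude for clinical diagnoses or for "psychological instability as identified by the meditation instructors", and the sentence goes on to say that screening instruments are used.
- If exclusions leave gaps, the sampling procedure is repeated to fill them in each group. Procedure also replaces dropouts to reach 100 per group.
- The pre-test comes after all of this: "This pre-intervention assessment period will last approximately 4 weeks".

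Study design and setting specifies computer-generated block randomisation at 1:1:1 and no blinding of participants or staff.

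**The concern.** Randomisation makes arms comparable on measured and unmeasured characteristics only for the people randomised. Here the analysed people are a subset, formed after allocation by the participant's own choice, by staff trimming and by an instructor's screen.

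The arms ask for very different things: daily disclosure to a partner who changes weekly, solitary meditation, or ten weeks of waiting. Willingness to accept each may well depend on loneliness, sociability or motivation. Loneliness is itself an outcome on which the protocol predicts an advantage for the socio-emotional arm.

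If willingness or exclusion depends on a trait that also predicts change, and does so differently by arm, part of the between-arm difference is selection rather than treatment. The self-reported pre-test is also collected after people have learned their arm, so the baseline may be affected by that knowledge.

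**Working it through.** **1. Filters after assignment.**

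| Step after random assignment | Who decides | Stated rule | Stated masking to arm |
|---|---|---|---|
| Interest after the webinar | Participant | None | No; arm introduced (Procedure) |
| Removal of surplus | Staff | Unspecified; aim is comparable groups | None |
| Screening call | Instructor | Two named instruments | None |
| Refilling gaps | Staff | Repeat the procedure, per group | None |

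Each filter can operate differently by arm. If the gaps are unequal, replacements directed at particular groups cannot follow 1:1:1 block allocation.

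**2. The plan's own sample size.** Inputs from Sample and sampling procedure: alpha 0.05, power 0.80, k = 3 groups, m = 2 occasions, correlation 0.39, f = 0.10. For the group-by-time interaction, λ = N·f²·m/(1 − ρ), with df 2 and N − 3. At N = 297, λ = 297 × 0.01 × 2/0.61 = 9.74 and power is 0.8002; N = 296 gives 0.7987. The stated 297 is reproduced, and N = 300 gives 0.8044. The issue is bias, which sample size does not address.

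**3. How many can be removed.** 3 × 200 = 600 assigned against 3 × 100 = 300 retained, so up to 300/600 = 50% if the final groups are drawn from full tentative groups.

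**4. Illustrative size of the bias.** The following assumptions are not in the documents. There is no true effect. A trait T has correlation r with the outcome, Y = rT + √(1 − r²)·e. Each arm is cut from 200 to 100. In one arm retention depends on T with log-odds slope b; in the other it does not depend on T. Two-sided test at 5%, 4,000 replicates.

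| r | b | Spurious difference (SD) | Type I error |
|---|---|---|---|
| any of 0, 0.2, 0.3, 0.5 | 0 | about 0 | 4.7% to 5.3% |
| 0 | 0.5 or 1.0 | about 0 | 4.7% to 5.0% |
| 0.2 | 0.5 | 0.05 | 6.0% |
| 0.2 | 1.0 | 0.08 | 9.2% |
| 0.3 | 0.5 | 0.07 | 8.6% |
| 0.3 | 1.0 | 0.12 | 14.7% |
| 0.5 | 0.5 | 0.12 | 12.9% |
| 0.5 | 1.0 | 0.21 | 32.4% |

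**5. Scale, taking Y as the change score.** On the change scale, f becomes 0.10 × √(2/0.61) = 0.181. If both training arms improve equally by d against control, f = d·√2/3, so d = 0.181/0.471 = 0.38 SD of change. Biases of 0.07 to 0.21 are then 0.07/0.38 = 18% to about 54% of the planned effect. The pairwise difference detectable with 80% power at 100 per arm is 2.80 × √(2/100) = 0.40 SD of change.

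**6. Can the analysis repair it?** The models use pre-test and post-test, with pre-test levels controlled through autoregressive paths. People removed before the pre-test have neither measurement, so the models cannot include everyone assigned. Adjustment for a baseline score handles selection on that score, but not selection on motivation or expected response.

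**The case against.** Several points on the other side stand.

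- The groups begin with computer-generated block randomisation, and the refill repeats a procedure that includes random assignment. A reader might infer that this is not a randomised trial or that its contrasts have no causal basis. The text does not support that; what is weakened is the protection randomisation gives.
- A reader might infer that half of those assigned leave by design after learning their arm. The figure of 200 is an ideal, trimming occurs only if interest exceeds 100, and some may decline because of dates or lab visits, or without attending.
- Arm disclosure at the webinar rests on Procedure alone.
- The screening call uses two standard instruments, so it is at least partly rule-based and should not be read as free discretion.
- Baseline and covariate adjustment deals with part of any stable difference; only traits related to change then bias the estimate.
- A sharp selection can be posited: keeping the whole upper half on a trait in one arm shifts its mean by 0.80 SD, and a correlation of 0.2 with change gives 0.80 × 0.2 = 0.16 SD. Nothing in the documents indicates selection that strong, so this is not a likely magnitude.

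It may also be said that an article condenses the trimming rule. But the order of steps is stated outright, and the only criterion given for trimming is a judgement about relevance and comparability. Making groups comparable on what staff can see does not balance what they cannot see. None of these points removes self-selection after disclosure.

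**Conclusion.** The concern holds in a limited form. Followed as written, the plan allows selection by arm at four steps between random assignment and the pre-test, and the analysis cannot fully undo it. The roughly 100 per arm analysed therefore start from a random draw but are no longer fully protected by it.

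The size of the bias is not determinable from the documents. The range of about 0.07 to 0.21 SD, with type I error of about 9% to 32%, assumes graded selection in one arm only, a trait–outcome correlation of 0.3 to 0.5 and log-odds slopes of 0.5 to 1.0. At a correlation of 0.2 it is 0.05 to 0.08 SD. It is nil if selection does not differ by arm or the trait is unrelated to the outcome. Because the main between-group conclusions rest on these contrasts and the repair is inexpensive, the order of steps should be changed wherever that is still possible.

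**What to change.** **For anyone not yet assigned.** Hold a common webinar covering all three conditions, then take consent, complete the screening call and preferably the pre-test, and only then randomise 1:1:1 in blocks and disclose the arm. The calculated N of 297 does not change.

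**For those already assigned** (Trial Status says the first pre-screened participant was invited to be informed on 27 May 2021):

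- replace the unspecified trimming criterion by a computer-generated random draw of the surplus within each arm;
- decide screening-call eligibility without sight of the allocation;
- randomise replacements 1:1:1 rather than by group gap, accepting slightly unequal final sizes;
- report participant flow and phase-1 characteristics by arm for everyone assigned. Phase-1 data exist for all 3522 people invited, so this needs no new data collection.

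This second set removes selection by staff and instructors and makes self-selection visible, but does not undo it; the report should say so.

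**Cost.** Protocol wording and a notification to the ethics committee. If the pre-test precedes randomisation, arms are disclosed about four weeks later, so training and coaching must be scheduled later. People who dislike their arm will then count as dropouts after randomisation and cannot simply be replaced. The target of 300 exceeds the required 297 by only three, so the sponsor should consider whether that margin is enough. Such dropouts would at least have a pre-test and be visible in the analysis.
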